**Table 1 Tab1:**
[figure not shown]
Measurements at each time-point of the study

T* birth outcomes PERINED data ^a^Part 2 of the Tic-P with questions regarding psychotropic drug use and psychosocial support. ^b^Case report form completed by e-mail counselors during intervention period

### Secondary outcomes

The following secondary outcomes will be obtained from participants. The exact time of administration can be found in Table 1.

Quality of life will be assessed with the Dutch version of the Short-Form 12 item Health Survey (SF-12) [53] and during the intervention with the one-item version of the Patient Global Impression of Change scale (PGI-C) [46].Care use will be assessed with part two of the Trimbos/iMTA questionnaire of the Costs associated with Psychiatric Illness (TiC-P) [54].State anxiety will be assessed with the 6-item STAI-State (i.e. the STAI-S) [55]. The 6-item STAI-S was constructed and validated previously [56, 57].Pregnancy specific anxiety will be assessed with the revised 10-item version of the Pregnancy Specific Anxiety Questionnaire-Revised (PRAQ-R2) suitable for both primi- and multiparous women [58].PTSD symptoms will be assessed with the 24-item Traumatic Event Scale-B (TES-B) specified to childbirth as the traumatic event [59].Mother-to-infant bonding will be assessed with the 5-item Prenatal and Postnatal Bonding Scale (PPBS) [60].Experience of childbirth will be assessed with the 22-item Childbirth Experience Questionnaire (CEQ-2) [61].Questions concerning breastfeeding and work resumption (T3 and T4) are based on the DELIVER study and have been adapted by the research team [62].The Dutch 3 and 4 months version of the Ages and Stages Questionnaires-3 (ASQ-3) will be used to assess five infant developmental domains: Communication, Gross Motor, Fine Motor, Problem Solving, and Personal Social [63, 64].The revised version 37-item version of the Infant Behaviour Questionnaire (IBQ-R) will be used to assess the infant’s temperament, as reported by the mother. The IBQ-R items were slightly changed to make it available for assessment of 6-week old infants [65, 66].Obstetric variables such as birth weight and preterm birth will be extracted from the Perinatal Registry database of the Netherlands [37].

### Mediators/moderators

Psychological flexibility will be assessed with the Dutch version of the 7-item Action and Acceptance Questionnaire-II (AAQ-II) [67].Mindfulness will be assessed with the Dutch version of the 14-item short form of the Freiburg Mindfulness Inventory (FMI-SF NL) [68].Coping with negative life events over the past year will be assessed with the Cognitive Emotion Regulation Questionnaire (CERQ) [69].COVID-19 related events experienced by (pregnant) women will be assessed with three closed questions about women’s health, the health of close relatives and financial setbacks, and three closed questions regarding the peripartum maternity care received.A potential (posttraumatic) stress reaction due to events like the COVID-19 crisis will be assessed with the Primary Care PTSD Screen for DSM-5 (PC-PTSD-5) validated in Dutch [70, 71].Satisfaction with obstetric care will be assessed with the 11-item Pregnancy and Childbirth Questionnaire (PCQ) validated in Dutch [72].Physical activity during pregnancy will be assessed with the short-form of the international physical activity questionnaire (IPAQ) [73].To assess satisfaction with the intervention, the Dutch version of the 8 item Client Satisfaction Questionnaire-8 will be used [74–76].To assess the (cumulative) cortisol concentration, hair samples will be weighted, cut with surgical scissors, and washed with 1.0 mL of LC-MS grade isopropanol for 2 min. The extraction of cortisol will be achieved by overnight incubation with methanol and analyzed with the LC-MS/MS grade including matrix interferences [77].

### Sociodemographic and medical variables

Sociodemographic and medical variables (T1) (e.g., smoking, alcohol use, age, parity, SES, ethnicity, gestational age, height and pre-pregnancy weight status, and work status) will be assessed with the pregnancy-adjusted Rotterdam Quality of Life interview [78] and using items derived from the DELIVER study [62].

## Statistical methods

### Power calculation

The medium effect (Cohen’s d) of ACT treatment on depressive symptoms lies between 0.4 and 0.6 [30, 79]. With a significant α level of 0.05 and 80% power we have to include 290 women to detect a small to moderate effect size (Cohen’s d) of > 0.33 between intervention and control group. Based on previous ACT-trials with similar (or even smaller) sample sizes of non-pregnant moderately depressed individuals, a Cohen’s d of at least 0.57 was found with largest Cohen’s d for women with increased depression levels at baseline [45, 80]. Assuming an attrition rate of 18% as in previous trials evaluating the long-term effectiveness of ACT [45, 80], the current sample-size allows us to detect small to moderate effect sizes (i.e., d = 0.365) with a power of 80% at the planned follow-up assessment [81]. We aim to include approximately 60 midwifery practices that will approach about 6,000 pregnant women, for participation. Based on an estimated response of 62% [62], we will be able to enroll approximately 3500 women in the cohort study of whom ca. 15% will have depressive symptoms [82]. Of these potential trial participants, 20% and 25% are expected to refuse participation or will be excluded, respectively, arriving at about 290 pregnant women with depressive symptoms to be included in the RCT.

### Statistical analyses

Analyses for the RCT will be done on both intention to treat (ITT) and per-protocol basis. First, to assess differences in depressive symptoms (EPDS) and resilience (i.e., well-being assessed with the MHC-SF) between intervention and control condition, independent t-tests will be used. The mean change of scores (T2-T1) will be standardized to interpret effect sizes in terms of Cohen’s d [83]. Next, ITT analyses will be performed using linear mixed modeling (LMM) to adequately deal with repeated measures data and clustering (i.e., at midwifery practice level). LMM’s with time, treatment, and time-by-treatment interactions will be performed to assess the intervention’s effectiveness in improving continuous primary outcomes of depressive symptomatology, resilience, and continuous secondary outcomes such as infant developmental milestones. Chi-square tests will be performed to assess group differences according to dichotomous (secondary) outcomes such as subclinical depression and flourishing incidence. Subsequently, generalized (binary) linear mixed models (GLMM) will be used to assess the intervention’s effect on the dichotomous secondary outcomes. To identify predictors of successful resilience training, (generalized) linear mixed models will be used. A multivariable GLMM to identify potential predictors of treatment success will be conducted in two steps: (1) univariable analyses to examine whether the potential predictor is significantly associated with the dichotomous outcome and (2) including significant predicting variables (*p* < .10) in the final multivariable model to identify independent predictors using the forward selection procedure. Finally, moderation and mediation analyses will be conducted to explore possible working mechanisms (psychological flexibility and mindfulness) of the intervention on maternal depressive symptomatology, resilience, and behavioral and infant developmental outcomes.

For the longitudinal data, latent class analyses will be used to explore different trajectories of depressive symptoms based on four repeated assessments over time. Correlates (e.g., cortisol levels) of perinatal depressive trajectories over time will be identified by using (generalized) linear mixed models. Associations between prenatal resilience and maternal mental health outcomes, birth, and infant developmental outcomes will be examined by using linear mixed models and GEE-analyses. All (main) analyses will be adjusted for potential confounders such as parity, educational level, and ethnicity. Multiple imputation methods will be used to impute missing values if missing at random can be assumed.

Audio-recorded qualitative interviews will be transcribed and anonymized. Transcripts of the interviews will be coded in an open, axial, and selective manner. Thematic analysis will be performed by two researchers [84]. After coding the first 3 or 4 interviews separately, both researchers will discuss the findings to modify the coding process. The software program MAXQDA will be used to facilitate the analysis process.

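### Neither the t-tests nor the mixed model names the baseline score as a covariate, so the planned treatment comparison gives up precision that baseline EPDS would supply at no cost

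*Protocol article*

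**What the plan says.** The Statistical analyses section of the protocol article gives two analyses of the same effectiveness question, in sequence.

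- First, for EPDS and MHC-SF: "between intervention and control condition, independent t-tests will be used". The next sentence standardises the mean change from T1 to T2 as Cohen's d.
- Next, on an intention-to-treat basis, linear mixed models "with time, treatment, and time-by-treatment interactions will be performed to assess" effectiveness on the continuous outcomes, also allowing for clustering by midwifery practice.

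In the following paragraph, which opens with the longitudinal cohort analyses, comes the adjustment sentence: "All (main) analyses will be adjusted for potential confounders such as parity, educational level, and ethnicity".

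The Power calculation section states: "With a significant α level of 0.05 and 80% power we have to include 290 women" for an effect "of > 0.33 between intervention and control group". It adds that d = 0.365 is detectable with 80% power after 18% attrition. It gives no correlation between T1 and T2, and does not say which SD scales d.

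EPDS is the screening instrument at T0 and a primary outcome. The Primary outcomes section lists MHC-SF at T2 to T4.

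**The concern.** In a randomised trial, covariates are worth including for their prognostic value, since allocation already deals with confounding in expectation. The earlier measurement of the outcome is the obvious candidate, and for EPDS two are available before treatment starts. The three adjustment variables that are named are demographic and obstetric.

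At stake is efficiency, not bias. A change score takes the baseline away with a coefficient of 1, whatever the data say the coefficient should be. A t-test on T2 scores uses a coefficient of 0. Either way the confidence interval is wider than the same 290 women allow. The mixed model looks like the remedy, but with T1 among the outcomes and a free treatment effect at T1 it estimates the same difference in changes.

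**Working it through.** **1. The plan's own figures.** Inputs from Power calculation: alpha 0.05 (sidedness not stated; two-sided assumed), power 80%, d = 0.33; 1:1 allocation from Study procedure.

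- n per arm = 2(1.960 + 0.842)² / 0.33² = 144.1, rounded up to 145, total 290. The exact t calculation gives 145.1 per arm. A one-sided test would need only 114 per arm (228 in total), so two-sided is what was used.
- After 18% attrition: 290 × 0.82 / 2 = 118.9 per arm. The exact t calculation gives a detectable d of 0.365.

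Both stated figures reproduce as a plain two-sample t-test with SD 1.

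**2. Variance of the three estimators.** Take a common SD of 1 at T1 and T2 and a within-arm correlation r (not in the documents; a range is assumed). Residual variances are:

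- T2 score: 1
- change score: 2(1 − r)
- ANCOVA on the T1 score: 1 − r²

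Hence ANCOVA/change = (1 + r)/2 and ANCOVA/T2 score = 1 − r².

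| r (assumed) | ANCOVA / change | ANCOVA / T2 score |
|---|---|---|
| 0.3 | 0.65 | 0.91 |
| 0.4 | 0.70 | 0.84 |
| 0.5 | 0.75 | 0.75 |
| 0.6 | 0.80 | 0.64 |
| 0.7 | 0.85 | 0.51 |

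Without equal variances, the change-score variance exceeds the ANCOVA variance by Var(T1)(1 − b)², where b is the slope of T2 on T1. This is never negative. The cost of ANCOVA is one degree of freedom.

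**3. Does the mixed model recover the loss?** In one simulated complete data set (290 women, T1 and T2, r = 0.4, time × treatment with a free main effect), the interaction was −0.268 (SE 0.126). The difference in mean change was also −0.268 (SE 0.126). It is the same contrast.

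**4. What this means for power**, at 145 per arm and d = 0.33 (normal approximation, equal variances):

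| r | Change, d in raw-score SD | ANCOVA, d in raw-score SD | Change, d in change SD | ANCOVA, d in change SD |
|---|---|---|---|---|
| 0.3 | 66% | 84% | 80% | 94% |
| 0.4 | 73% | 87% | 80% | 92% |
| 0.5 | 80% | 90% | 80% | 90% |
| 0.6 | 88% | 94% | 80% | 88% |
| 0.7 | 95% | 98% | 80% | 86% |

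A t-test on T2 scores with d in raw-score SD has 80% at every r. ANCOVA is the higher in every row. The change-score test falls below 80% only if d is in raw-score SD and r is under 0.5.

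**5. Effect of selecting on T0.** Entry at EPDS ≥ 11 selects about the top 15% (the rate in Power calculation). For a normal score, the cut is z = 1.036, the selected mean is 1.554, and k = 1.554 × (1.554 − 1.036) = 0.805. With assumed population correlations T0–T1 = 0.7, T0–T2 = 0.5 and T1–T2 = 0.6:

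- Var(T1) = 1 − 0.805 × 0.49 = 0.606
- Var(T2) = 1 − 0.805 × 0.25 = 0.799
- Cov = 0.6 − 0.805 × 0.35 = 0.318, so r = 0.46
- Var(change) = 0.606 + 0.799 − 0.636 = 0.768, which is 0.96 of Var(T2)

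With d in T2 SD, change-score power is 82% and ANCOVA power 88%; the variance ratio is 0.82. With 0.8/0.6/0.7 the powers are 88% and 91%. With 0.6/0.5/0.5 they are 71% and 85%. Selection lowers r, but it also shrinks Var(T1), and the two effects pull change-score power in opposite directions.

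**The case against.** The strongest reply is that every listed analysis is valid under randomisation, that this is a condensed article, and that covariates and the deciding contrast are often left to an analysis plan. The adjustment sentence also introduces its list with examples, so a baseline score is not excluded. All of that is fair and limits the point to efficiency. It does not remove it: the article does specify the estimators and typical covariates, and these leave out the most useful one.

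Several stronger readings are tempting and are not supported:

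- *The trial is underpowered.* The sample size reproduces. A shortfall needs d in raw-score SD and a low r with near-equal variances. The documents give neither r nor the SD scale, and standardising the change suggests that d may be on the change scale, where power stays at 80%. The plan also cites ACT effects of 0.4 to 0.6, above the 0.33 used here.
- *Selection on T0 drives power far down.* Step 5 shows that it can leave change-score power above or below 80%, depending on correlations that nobody has stated.
- *The t-test is the primary analysis, it is run on change, and it is unadjusted.* The text says only that t-tests come first and the mixed model next. The change is mentioned for the effect size, so its use in the test is an inference. The adjustment sentence may cover the trial, though its scope is unclear.
- *The mixed model necessarily repeats the change-score contrast.* That requires T1 to be an outcome, which is not stated. The same sentence covers infant milestones, which can have no T1 value.
- *Effectiveness rests on a joint interaction test over all time points.* The article specifies no such test.

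**Conclusion.** The point stands as a matter of precision. No analysis in the article names the baseline outcome score, and adding it reduces the variance whether the t-test is on change or on T2 scores. Against the change score, the variance ratio is 0.65 to 0.75 for r of 0.3 to 0.5 with equal variances. In the three selected-sample examples it is between 0.71 and 0.89. That the mixed model fails to recover this is conditional on T1 being in the outcome vector with a free treatment effect.

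The stated 290 and 0.365 are correct for the two-sample test that they describe. Power under 80% is a possibility that depends on unstated inputs, not a finding. All values of r are assumptions.

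For MHC-SF the benefit cannot be claimed yet: the Primary outcomes section lists T2 to T4, while Statistical analyses takes a change from T1. As written there is no T1 value to subtract or to adjust for.

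**What to change.** 1. Name one primary analysis: an intention-to-treat linear mixed model with categorical time and practice clustering as planned. Either enter T1 EPDS (optionally also T0) as a covariate with T2 to T4 as outcomes, or keep T1 as an outcome with the arms constrained equal there.
2. Report the treatment contrast at T2 as the primary estimate, with T3 and T4 contrasts from the same model.
3. Keep the t-tests as description only.
4. State the SD used for Cohen's d, in the power calculation and in the analysis, and the T1–T2 correlation assumed.
5. Say whether the adjustment sentence applies to the trial, and add the baseline score to it.
6. For MHC-SF, reconcile the T2–T4 schedule with the T1-to-T2 change, checking Table 1. Adjust for its T1 score if it is collected, otherwise for T1 EPDS.

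For EPDS this is a change of wording only, with no extra data or visits. With 60 women in the RCT when the article was written, it could be made well before analysis. For MHC-SF the cost depends on whether a T1 measurement exists; adjusting for T1 EPDS needs none.

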### Participants, eligibility, and screening

Women are eligible to participate when aged ≥ 18 years, receiving antepartum care at the moment of inclusion. Women will be excluded when they do not master the Dutch language sufficiently. After informed consent, all women will participate in a screening procedure for depressive symptoms (T0; 12–18 weeks gestation) and subsequent online assessments throughout pregnancy and postpartum (Fig. 1; T1 – T4).

For the embedded RCT, an additional inclusion criterion is an EPDS score of ≥ 11 [38] with or without a mild depressive disorder (i.e. a subclinical depression) as based on a structured clinical interview by telephone assessing the presence and severity of current depressive or dysthymic disorders and suicidality with the Mini International Neuropsychiatric Interview (MINI) supplemented with the Sheehan Disability Scale (SDS) [39–41]. The RCT’s exclusion criteria are psychopharmacological and/or psychological treatment over the past three months (reported by the participant), a current major depressive disorder, and/or moderate to high suicide risk (based on the MINI).

Additional inclusion criteria for the HCC sub-study are willing to provide a hair sample and sufficient hair growth at the posterior vertex of the head with a length of at least 1 cm. Women who used oral corticosteroids in the previous 3 months will be excluded from participation in the HCC sub-study.

For the qualitative sub-study, participants in the RCT will be purposively sampled from the intervention group to assess the self-help resilience training experiences. We will include a sample of ca. 20 women. The sample consists of women with improved EPDS scores (< 11) and women with continued depressive symptoms at T2 (EPDS score ≥ 11) as well as women who did or did not complete the full training and modules of the intervention.

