### Study procedure

After providing and receiving informed consent, all participants will be screened for depressive symptoms through online completion of a digital version of the EPDS and, if the score is ≥ 11, followed by a 10–15 minutes telephone interview (MINI) to assess the severity of the depressive symptoms and to assess whether the participant meets DSM-5 criteria for current depressive or dysthymic disorders and suicidality. Master’s students in clinical or research psychology will conduct interviews. A healthcare psychologist with expertise in treating women in the antepartum and postpartum period will train the students.

In line with international guidelines for psychosocial care (NICE-Guideline, 2014) and from a medical-ethical perspective, all participants will receive feedback about their EPDS symptom level and, if applicable, about the psychiatric telephone-interview outcome. A copy of the two-step screening procedure results will also be shared with the participants’ midwife or obstetrician (for which participants gave informed consent). Midwives or obstetricians will be advised to discuss the outcome with their client and further monitor their client’s symptoms if screening results indicate a subclinical depression. If the MINI psychiatric interview identifies (suspected) major depressive or dysthymic disorder or suicidal ideations, they will be advised to refer women to specialized mental healthcare.

To randomly allocate pregnant women with subclinical depression to the intervention or control condition for the RCT, an independent statistician from the department of Epidemiology and Biostatistics (VUmc) will provide a computer-generated blocked randomization sequence in a 1:1 ratio, stored in individual sealed opaque envelopes. Block sizes will be undisclosed to ensure concealment. Following each RCT inclusion, a research assistant will open the next envelop and allocate the participant to the intervention or control condition. After randomization, participants in the control condition will be informed by mail that they will receive care as usual from their midwife or obstetrician. Participants randomized to the intervention condition will receive the ACT-based self-help book and its pregnancy adapted supplement.

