## Assessments

### Primary outcomes

Depressive symptoms will be assessed with the 10-item Edinburgh Postnatal Depression Scale (EPDS) [47, 48]. The EPDS has been validated to screen for mild or major depression both antepartum and postpartum [49]. A Dutch validated EPDS version with good internal validity with a Cronbach’s alpha of 0.83 [48] and good concurrent and predictive validity is available [38]. The ten items’ response options range from 0 to 3, with higher scores indicating more depressive symptoms. For inclusion, a cut-off of ≥ 11 will be used since sensitivity and specificity for depression at this cut-off are estimated to be 0.83/0.90 in the antepartum period [18, 38, 50].

Resilience will be measured with the Dutch version of the Mental Health Continuum-Short Form (MHC-SF) (T2-T4; Table 1). Mental health or well-being acts as a resilience resource that buffers against psychopathology. The MHC-SF has 14 items that are scored on a 6-point scale ranging from 0 to 5 (never, rarely, sometimes, regularly, often, or (almost) always) and captures three dimensions: emotional (3 items), psychological (6 items) and social well-being (5 items) over the past 4 weeks. The Dutch version has shown good psychometric properties, is reliable (internal reliability of alpha 0.89 on MHC-SF total; and alpha’s of resp. 0.83, 0.83, and 0.74 on emotional, psychological, and social well-being subscales resp.) and was validated in a Dutch sample (n = 1621) [51]. With the MHC-SF, well-being can be distinguished into flourishing, neither flourishing nor languishing, and languishing (i.e., absence of well-being) [52].

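### The one predictor procedure spelled out selects on a dichotomous, undefined treatment success; if that is a cut of the EPDS or MHC-SF score, it wastes information the trial already collects

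*Protocol article*

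**What the plan says.** In the protocol article, *Statistical analyses* uses linear mixed models for the treatment effect on depressive symptoms and resilience, and calls both outcomes continuous. The EPDS is a summed scale: "The ten items’ response options range from 0 to 3, with higher scores indicating more depressive symptoms" (*Primary outcomes*), so ten items give a total of 0 to 30.

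For predictors, the same section first names mixed models in general, with the word generalized in brackets. It then sets out one concrete procedure: "A multivariable GLMM to identify potential predictors of treatment success will be conducted in two steps". Step 1 is "univariable analyses to examine whether the potential predictor is significantly associated with the dichotomous outcome". Step 2 takes the variables with p < .10 into a multivariable model with forward selection.

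Treatment success is not defined. Two other places bear on its meaning:

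- *Statistical analyses* gives subclinical depression and flourishing as examples of dichotomous secondary outcomes.
- *Participants, eligibility, and screening* describes the interview sub-study: "The sample consists of women with improved EPDS scores (< 11) and women with continued depressive symptoms at T2 (EPDS score ≥ 11"). Improved is tied to a cut of 11 there, for sampling about 20 women.

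**The concern.** A predictor that misses the step 1 threshold on the dichotomous outcome never reaches the final model, so the outcome scale decides what can be found. The data for this question are limited: 290 women in all, or 145 if only the intervention arm is used. Replacing a score by a yes/no cut discards information, and real predictors of who does well may be missed.

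If success means EPDS below 11, there is a second difficulty. An EPDS of 11 or more is the entry criterion for the randomised trial, so all randomised women screened at or above that line. A woman going from 11 to 10 would then be a success and one going from 22 to 12 a failure. Success would partly record how near the line she started. *Primary outcomes* supports the value 11 by its sensitivity and specificity as a cut for inclusion, not as a criterion of response.

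**Working it through.** **1. The plan's own figures.** *Power calculation* states "With a significant α level of 0.05 and 80% power we have to include 290 women" for an "effect size (Cohen’s d) of > 0.33 between intervention and control group", with 1:1 allocation (*Study procedure*). Two-sided:

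- Per arm: 2 × (1.960 + 0.842)² / 0.33² = 144.1, rounded up to 145, so 290 in total. Reproduced.
- After 18% attrition: 290 × 0.82 ≈ 238. Detectable d = (1.960 + 0.842) × √(4/238) = 0.363, against the stated 0.365. Reproduced.
- Intervention arm alone: 145 × 0.82 ≈ 119.

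These figures concern the treatment comparison. No success rate, predictor effect or analysis set is given for the predictor analysis, so those below are assumptions.

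**2. Information kept by a cut.** For a normal score cut so that a fraction p succeeds, the relative efficiency is φ(c)² / [p(1 − p)], where c is the cut point.

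- p = 0.50: 0.3989² / 0.25 = 0.64
- p = 0.30 or 0.70: 0.3477² / 0.21 = 0.58
- p = 0.20: 0.49

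**3. A check by hand.** Take a predictor that splits 290 women 50:50, with d = 0.33 and two-sided 0.05.

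- Continuous score: Φ(0.33 × √(290/4) − 1.960) = Φ(2.810 − 1.960) = 80.2%.
- Cut at 50% success: Φ(2.810 × √0.637 − 1.960) = Φ(0.282) ≈ 61%.
- Cut at 30% success: Φ(2.810 × √0.576 − 1.960) = Φ(0.172) ≈ 57%.

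The two-proportion formula gives 60.8% and 56.3%, a loss of 19.4 and 23.9 points.

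**4. Continuous predictor.** Simulation with 20,000 runs per cell: predictor and outcome bivariate normal with correlation r, one follow-up, complete cases, success 30%, 50% or 70%. A correlation test on the score is compared with the same test on the cut.

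| n | r | test level | power, score | power, cut | loss (points) |
|---|---|---|---|---|---|
| 119 | 0.25 | 0.05 | 79% | 55-59% | 19-24 |
| 119 | 0.25 | 0.10 | 87% | 67-71% | 16-20 |
| 119 | 0.20 | 0.05 | 59% | 38-42% | 17-21 |
| 119 | 0.30 | 0.10 | 96% | 80-84% | 11-15 |
| 238 | 0.20 | 0.05 | 87% | 65-70% | 18-22 |
| 238 | 0.20 | 0.10 | 93% | 76-80% | 13-17 |
| 238 | 0.25 | 0.10 | 99% | 91-93% | 6-8 |
| 238 | 0.30 | 0.05 or 0.10 | over 99% | 95-98% | 2-5 |

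A likelihood-ratio logistic test on the cut moves individual cells by a few points and leaves the pattern unchanged. The loss is largest where the score itself has moderate to good power, and small where power is already near 100%. At 20% success it is larger: 26 to 32 points for effects that the score would detect with about 80-88% power.

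**The case against.** Much of the case for leaving the text alone is fair.

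- **Definition of success.** A reader might infer that success is EPDS below 11. The document does not say so: that cut labels women as improved only for interview sampling, and the two dichotomous outcomes are named as examples. A responder definition based on change would not behave like the 11-to-10 versus 22-to-12 example. This stands, so that example is conditional. An exact definition may also sit in a fuller document.
- **Continuous model not excluded.** A reader might infer that predictors will be sought on the binary outcome only. The bracketed word generalized leaves room for a linear model. This also stands. Even so, the procedure actually set out, with its screen and selection rule, rests on the dichotomy in both steps, and no continuous counterpart is described.
- **Baseline severity.** Screening EPDS would be expected to predict a continuous follow-up score too, and it could be added to the binary model. Adjustment is therefore not what separates the two approaches; the information lost by the cut is.
- **Simplified calculation.** The plan has repeated measures, clustering by midwifery practice and multiple imputation, and it does not restrict this analysis to intervention-arm completers. The figures show the order of magnitude, not the power of the planned model.
- **Clinical meaning.** Who falls below a recognised threshold is a legitimate question. It can be answered from a continuous model as a secondary display.

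**Conclusion.** The point holds in a limited form. The only predictor procedure described selects on a dichotomous outcome whose definition is not given, while the likely underlying scores are collected and modelled as continuous elsewhere in the same section.

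If success is a cut of one of those scores, 36-42% of the information is lost at 30-70% success. Under bivariate normality and a single follow-up, the cost in power is about 15-24 points for n = 119 with r = 0.20-0.25, about 13-23 points for n = 238 with r = 0.20, and about 2-5 points for n = 238 with r = 0.30. A blanket claim of at least 15 points would be wrong, because sample, correlation and success rate are all assumed.

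Nor should a reader infer any weakness in the primary treatment comparison, which uses the continuous scores. This is a worthwhile improvement to a supplementary analysis.

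**What to change.** In *Statistical analyses*:

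- Make the continuous follow-up EPDS and MHC-SF scores the outcomes on which predictors are identified. Use the linear mixed model already planned, with the screening (T0) EPDS in the model.
- Define treatment success explicitly.
- Report the binary results, for example EPDS below 11 and flourishing, as a secondary and descriptive translation of the fitted model.

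The cost is a change of wording, with no new data and no additional participants. The small downside is that predictor effects appear in scale points, with success probabilities shown secondarily.
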